### Statistical analysis

Descriptive statistics will be used to present group characteristics at baseline; to compare study completers with participants who discontinued the study; and to compare participants with good training completion with those with poor training concordance. Training-safety data will be summarized descriptively and compared against pre-set safety parameters (standard safe ranges of vital parameters as used in clinical practice).

Inferential statistics will be used to evaluate the effect of treatment on the primary and secondary outcome parameters. The hypotheses under investigation are as follows: RMT (inspiratory or expiratory) is effective for improving voluntary cough effectiveness (voluntary cough PECF); RMT (inspiratory or expiratory) is effective for improving reflex cough effectiveness (reflex cough PECF); expiratory muscle training is effective for improving expiratory muscle strength (MEP); inspiratory muscle training is effective for improving inspiratory muscle strength (MIP); RMT (inspiratory or expiratory) is effective for reducing the incidence of pneumonia.

The sample-size calculation followed an ANOVA model of inferential statistical analysis. However, it is anticipated that the study sample will show considerable heterogeneity, in which case, an analysis of covariance (ANCOVA) model is more powerful in detecting a difference in study arms
[62]. ANCOVA will be used to compare group means of voluntary and reflex cough PECF, MEP, and MIP at the primary end point (day 29). The following covariates will be adjusted for: gender, age, smoking, stroke severity (NIHSS score), training intensity, and a predictor variable for “missingness”, which will be determined through logistic regression. Fisher Exact test will be used to compare the incidence of pneumonia from baseline through week 4 between the three study groups. Adjustments for multiple testing will be made by using the Benjamini-Hochberg method
[63].

Four approaches to dealing with missing values will be compared in a sensitivity analysis: intention-to-treat analysis, substituting missing values through predictive model-based imputation
[64]; intention-to-treat analysis, substituting missing values through propensity score imputation
[65]; intention-to-treat analysis, substituting missing values with baseline data; and complete case analysis, using only data from participants who completed the primary end point.

Further exploratory analyses may be conducted as thought appropriate, and any relevant findings will be reported accordingly.

The data-analysis plan has undergone some revision as the picture of the actual data observed became clearer with ongoing data collection, and it includes sensitivity and exploratory analyses. This flexible approach to data analysis is justified in this study, which is understood as a pilot project. Discovering what type of data can be expected in this population and comparing alternative statistical analysis approaches for these data falls within the aim of the project to inform the design of a larger clinical trial. However, the primary and secondary end points for the study have been clearly defined and have remained unchanged from the outset, and the results will be reported accordingly and in a transparent manner, regardless of “positive” or “negative” results. Although participant-level data will not be made publicly available, the data will be archived at the study center for 10 years according to regulatory requirements, where it will be available for scrutiny. Details of the statistical-analysis code will be included in the full study report.

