**Methods/design:**

Adults with moderate to severe stroke impairment (National Institutes of Health Stroke Scale (NIHSS) score 5 to 25 at the time of admission) are recruited within 2 weeks of stroke onset. Participants must be able to perform voluntary respiratory maneuvers. Excluded are patients with increased intracranial pressure, uncontrolled hypertension, neuromuscular conditions other than stroke, medical history of asthma or chronic obstructive pulmonary disease, and recent cardiac events. Participants are randomized to receive inspiratory, expiratory, or sham respiratory training over a 4-week period, by using commercially available threshold resistance devices. Participants and caregivers, but not study investigators, are blind to treatment allocation. All participants receive medical care and stroke rehabilitation according to the usual standard of care. The following assessments are conducted at baseline, 4 weeks, and 12 weeks: Voluntary and reflex cough flow measurements, forced spirometry, respiratory muscle strength tests, incidence of pneumonia, assessments of safety parameters, and self-reported activity of daily living. The primary outcome is peak expiratory cough flow of voluntary cough, a parameter indicating the effectiveness of cough. Secondary outcomes are incidence of pneumonia, peak expiratory cough flow of reflex cough, and maximum inspiratory and expiratory mouth pressures.

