### Sample size

The initial sample-size calculation was based on observations from a cross-sectional study of acute stroke patients
[44] and a one-way analysis of variance (ANOVA) model of statistical analysis
[60,61]. For group sizes of less than 50, ANOVA assumes that data are normally distributed and that variances are equal. For the purpose of this sample-size calculation, these assumptions were made. With an estimated group standard deviation (SD) of 50 L/min for the main outcome measure (voluntary cough PECF at the primary end point), a sample size of 16 subjects per group gives the study 80% power to detect a 50 L/min difference between groups at the 5% significance level. Assuming an attrition rate of 20%, 20 subjects per study group are required, giving a total sample size of 60.

The sample-size calculation was reviewed after the first 40 participants completed their participation in the study. At this point, participant attrition was higher than anticipated (32%), and primary outcome data showed greater variability than initially assumed, with group SD ranging from approximately 100 to 250. Table 
1 shows estimates of the required number of participants per group to give the study 80% power at the 5% significance level, according to different treatment-effect sizes and different group standard deviations. Taking into account these observed data, the decision was made to increase the study sample to 20 participants per group. This group size was selected to give higher statistical power should the data show large within-group variability. Also, it was considered a realistic recruitment target, given the observed rate of recruitment and the resources available. Taking into account a dropout rate of approximately 30%, the revised target sample is 90 subjects, whereby recruitment will be concluded early once 20 participants per group complete the primary study end point.

**Table 1 T1:** Sample-size calculation

**Expected treatment effect (L/min)**	**Expected SD within group (L/min)**					
	**50**	**100**	**150**	**200**	**250**	**300**
50	15	58	125	250	400	600
100	5	15	35	60	95	125
150	<5	8	15	26	42	58
200	<5	5	10	16	24	34

Estimates of required number of participants per study group to give 80% power at the 5% significance level, according to different expected treatment-effect sizes and different expected group standard deviations (SDs) of the primary outcome (peak expiratory cough flow (PECF) of voluntary cough).

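### The ANCOVA covariate list omits each outcome's own baseline value, although it is measured; adding it is a free gain in precision, and the planned analysis stays valid without it

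*Protocol article*

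**What the plan says.** The Statistical analysis section moves from the ANOVA used for sample size to ANCOVA. The reason given is that the sample is expected to be heterogeneous, in which case "an analysis of covariance (ANCOVA) model is more powerful in detecting a difference in study arms". The model and outcomes are then fixed: "ANCOVA will be used to compare group means of voluntary and reflex cough PECF, MEP, and MIP at the primary end point (day 29". So are the covariates: "The following covariates will be adjusted for: gender, age, smoking, stroke severity (NIHSS score), training intensity, and a predictor variable for" missingness. The outcome is the day-29 level, not change from baseline, so the baseline value does not enter indirectly.

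The baseline values exist. The abstract states: "The following assessments are conducted at baseline, 4 weeks, and 12 weeks: Voluntary and reflex cough flow measurements, forced spirometry, respiratory muscle strength tests". In the Statistical analysis section, baseline data as outcome values appear only in one of the four missing-data approaches: "intention-to-treat analysis, substituting missing values with baseline data".

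On variability, the Sample size section begins "With an estimated group standard deviation (SD) of 50 L/min for the main outcome measure", then reports that after 40 participants "primary outcome data showed greater variability than initially assumed, with group SD ranging from approximately 100 to 250". The section on randomization describes blocks of 12 and mentions no stratification by cough function.

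**The concern.** ANCOVA was chosen to gain power in a heterogeneous sample. A participant's own earlier value on the same measure is the natural covariate for that purpose, and it is the one left out. With an observed SD two to five times the planned 50 L/min and about 20 completers per arm, precision is scarce. Objective (a) of the pilot is to estimate the magnitude of effect for a larger trial, so a needlessly wide interval bears directly on the study's aim.

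The described allocation does not balance baseline cough function either. At this size, arms can differ appreciably at baseline by chance, and the planned model removes only the part of that difference that gender, age, smoking, NIHSS score and the other listed terms happen to predict.

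**Working it through.** **1. The plan's own figure.** Inputs from the Sample size section: difference 50 L/min, SD 50 L/min, 5% level (taken as two-sided), 80% power.

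n per group = 2 × (1.960 + 0.842)² × 50²/50² = 15.7, so 16, as stated. One-way ANOVA with 16 per group and means 0, 50, 50 gives 81.4% power. Allowing for 20% attrition, 16/0.8 = 20 per group, also as stated. The sample-size calculation used no covariates, so the omission does not make it wrong.

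**2. Effect of adding the baseline, against a model with no covariates.** Let r be the correlation between baseline and day 29. It is not given, so 0.3 to 0.8 is assumed. Residual variance becomes SD² × (1 − r²). Power comes from the three-group F test with one arm d apart from the other two:

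λ = n × (2/3) × d² / [SD² × (1 − r²)], with n = 20 and 2 and 57 degrees of freedom.

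Example: d = 100, SD = 150, r = 0 gives λ = 20 × 0.667 × 10,000/22,500 = 5.93 and power 55%. With r = 0.7, λ = 5.93/0.51 = 11.62 and power 85%.

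| r | 1 − r² | Equivalent n, 20/(1 − r²) | Power: d 100, SD 150 | Power: d 50, SD 100 | Power: d 100, SD 250 |
|---|---|---|---|---|---|
| 0 | 1.00 | 20 | 55% | 34% | 23% |
| 0.3 | 0.91 | 22 | 60% | 37% | 25% |
| 0.5 | 0.75 | 27 | 69% | 44% | 29% |
| 0.7 | 0.51 | 39 | 85% | 60% | 41% |
| 0.8 | 0.36 | 56 | 95% | 76% | 55% |

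Charging seven residual degrees of freedom for covariates lowers these figures by less than one percentage point. A simulation of pairwise comparisons (d 50, SD 100, 20 per arm, 4,000 runs) agreed with the pairwise formula: about 34% without the baseline, and 43%, 57% and 72% with it at r = 0.5, 0.7 and 0.8.

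**3. Against the model actually planned.** The plan already adjusts for other covariates, so the relevant quantity is the partial correlation given those covariates. Suppose they explain a share R of the variance at both baseline and day 29 through the same linear combination (R = 0.2 or 0.3, assumed). Then

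partial r = (r − R)/(1 − R), and residual variance = SD² × (1 − R) × (1 − partial r²).

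For d = 100, SD = 150, 20 per arm:

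| R | Power, listed covariates only | Adding baseline, r = 0.5 | Adding baseline, r = 0.7 |
|---|---|---|---|
| 0.2 | about 65% | about 72% (partial r 0.375) | about 87% (partial r 0.625) |
| 0.3 | about 72% | about 76% (partial r 0.286) | about 88% (partial r 0.571) |

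The gain is about 4 to 7 points at r = 0.5 and 16 to 21 points at r = 0.7. With R = 0.3 and r = 0.3 the partial correlation is zero and nothing is gained.

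**4. Chance imbalance.** If the baseline SD resembles the day-29 SD (assumed), the difference in baseline means between two arms has standard error SD × √(2/20): 32 L/min at SD 100 and 79 L/min at SD 250. With equal SDs, a baseline difference carries into the day-29 contrast multiplied by r. At r = 0.7, a one-standard-error imbalance shifts the contrast by 0.7 × 32 = 22 L/min or 0.7 × 79 = 55 L/min; at r = 0.3, by 9 or 24 L/min. These are upper figures, because the listed covariates absorb some of the shift.

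**The case against.** A reader might infer that the planned comparison is biased, or that any baseline imbalance passes in full into the estimated effect. The documents do not support that. Randomization keeps the estimate unbiased over repeated trials, and omitting a baseline covariate does not inflate the type I error. An imbalance in a particular sample is scaled by the regression slope and partly absorbed by the listed covariates.

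A reader might also take the rise from 55% to 85% as the loss caused by the plan. Its starting point is a model with no covariates, which is not planned, and its end point assumes r = 0.7. Baseline falls within two weeks of an acute stroke, when recovery may vary, and two recording systems are in use, so a low r cannot be excluded. Nor does the fix rescue power generally: for the originally planned 50 L/min effect at SD 100, power stays below 80% even at r = 0.8.

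It can be said that this is a pilot with room for exploratory analyses, so a baseline-adjusted result could be reported anyway. That is true, but it would not place the baseline in the primary model. The article also says that the plan was revised as data accrued, so a covariate added after results are known would be open to question. The omission cannot be read as left to a separate analysis plan, because the article itself states the list.

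One caution on the fix: the investigator opens the allocation envelope immediately before the baseline session and so measures baseline knowing the arm. Adjustment assumes that the baseline tests precede any training and are not influenced by that knowledge.

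What stands is the omission and the loss of precision. What does not stand is any claim that the analysis is invalid.

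**Conclusion.** The point holds as a worthwhile free improvement. The stated covariate list leaves out a measured variable that serves the plan's own reason for choosing ANCOVA. The cost is precision, plus chance baseline imbalance that is only partly corrected.

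The size is uncertain. For 20 per arm, a 100 L/min effect and SD 150 L/min, the gain over the listed covariates could be a few points of power or about 20. It rests on two quantities the article does not give: the baseline to day-29 correlation, and the share of variance the listed covariates already explain. None of the figures counts any loss from adjusting for training intensity, which the Intervention section sets differently by arm (50% versus 10% of maximum mouth pressure). That is a separate issue.

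**What to change.** Before the analysis is run, amend the covariate list so that the primary ANCOVA includes baseline voluntary PECF, and each secondary ANCOVA includes the baseline of its own outcome: reflex PECF, MEP or MIP. Date the amendment and record that it was made before day-29 results were compared by arm.

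The cost is a change of wording and one residual degree of freedom per model. No further data or participants are needed. Reporting the observed baseline to day-29 correlation would also give the larger trial a planning figure that the article lacks.

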### Aims and objectives

The present study investigates whether RMT is a worthwhile treatment approach to pursue for the reduction of pneumonia rates in acute stroke patients. The aim is to provide estimates on its magnitude of effect, acceptability, safety, and feasibility, and to inform about the value and design of a large clinical trial. The study objectives are (a) to determine the magnitude of effect of the intervention on cough generation, respiratory muscle strength, and incidence of pneumonia; (b) to explore the training duration, frequency, and intensity required to achieve improvement in cough flow and inspiratory and expiratory muscle strength; (c) to evaluate patient participation, acceptability of study procedures to participants, and concordance with training protocol; (d) to describe safety parameters and potential adverse effects of RMT in this patient group; (e) to describe characteristics of those patients most likely to gain from the intervention; and (f) to determine the relevance and feasibility of delivering RMT to acute stroke patients in a National Health Service (NHS) setting in the United Kingdom (UK).

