### Weaknesses

The methods for identifying the presence of swallowing difficulty and pneumonia in the current study may be regarded as a limitation. To minimize participant burden created by additional medical procedures, it was decided to take a pragmatic approach and observe clinical and self-reported information on swallowing function and pneumonia. A more-detailed instrumental assessment of swallowing, such as video-fluoroscopic examination of swallow, could be used to determine the degree of dysphagia and aspiration. Objective diagnostic criteria for pneumonia, including assessments of chest radiographs and blood results
[69,70], could be used to support the detection of pneumonia.

A further limitation to the study is the lack of investigator blinding. The investigator is masked to treatment-allocation sequence, but is aware of group allocation from the point of randomization.

Although the clinical purpose of this research is to reduce the risk of pneumonia after stroke, the study uses voluntary cough flow as a surrogate primary outcome. This surrogate outcome was selected to minimize the required sample size. Designing the study according to the primary outcome, pneumonia, would require a considerably larger sample. For example, it could be assumed that both intervention groups would show a reduction in pneumonia rates from 15% to 7.5% compared with the control group. To give 80% power at the 5% significance level, this would require approximately 180 participants per group (using the χ^2^ test and not accounting for attrition).

The choice of voluntary cough flow as a surrogate primary outcome in this study was based on the physiological rationale to the research. Also, good evidence shows that reduced voluntary cough flow in stroke patients is associated with higher risk of aspiration, and therefore aspiration pneumonia
[35,36]. To our knowledge, the direct relation between voluntary cough flow and pneumonia has not been investigated in stroke populations. The importance of cough flow may be inferred from populations with neuromuscular conditions, where reduced levels of voluntary cough flow indicate the need for assisted airway clearance

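### Pneumonia: the objective is the size of the effect, but the only treatment comparison stated is a three-group Fisher exact test, with about 7–12% power at the article's own example rates and no effect estimate or interval specified

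*Protocol article*

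**What the plan says.** Under Aims and objectives, the overall purpose is estimation: "The aim is to provide estimates on its magnitude of effect, acceptability, safety, and feasibility". Objective (a) includes pneumonia by name: "to determine the magnitude of effect of the intervention on cough generation, respiratory muscle strength, and incidence of pneumonia".

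Under Statistical analysis, inferential statistics are assigned to the primary and secondary outcomes. One of the five listed hypotheses is that "RMT (inspiratory or expiratory) is effective for reducing the incidence of pneumonia". The method given for it is: "Fisher Exact test will be used to compare the incidence of pneumonia from baseline through week 4 between the three study groups". A Benjamini-Hochberg adjustment follows. No effect measure or interval for pneumonia is named.

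Under Sample size, recruitment stops once 20 participants per group complete day 29, with a revised target of 90 randomised.

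Under Weaknesses, the article explains why pneumonia is not the primary outcome. It supposes that "both intervention groups would show a reduction in pneumonia rates from 15% to 7.5% compared with the control group" and concludes: "To give 80% power at the 5% significance level, this would require approximately 180 participants per group", by a chi-square test and without allowance for attrition.

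**The concern.** The stated method does not serve the stated objective. A three-group Fisher exact test asks whether the three incidences differ in any way at all. It has no direction, does not itself contrast RMT with sham, and gives no effect size. Objective (a) asks how large the effect is, and the listed hypothesis is directional.

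The article also acknowledges that a trial designed around pneumonia would need a considerably larger sample, yet its stated treatment analysis for pneumonia is still a hypothesis test.

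At stake is what the pilot hands on. It is meant to inform the value and design of a larger trial, and for that the planners need the incidence per arm and a difference against sham with its uncertainty. A p-value above 0.05 from so small a sample is compatible with a large benefit, no effect or some harm, and on its own it could be taken for evidence of no effect.

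**Working it through.** **Inputs (all from the protocol article)**
- Rates: 15% sham, 7.5% in each active arm (Weaknesses, the article's own illustration).
- Arm size: 20 completers per group, or 90/3 = 30 randomised per group (Sample size). Allocation is equal (blocks of 12, four per arm).
- Level: 5%.

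**Step 1. The article's own figure of 180 per group.** For a three-group chi-square test the pooled rate is (15 + 7.5 + 7.5)/3 = 10%. The noncentrality is n × Σ(pᵢ − 0.10)² / (0.10 × 0.90).
- Σ(pᵢ − 0.10)² = 0.05² + 0.025² + 0.025² = 0.00375, so the noncentrality is n × 0.00375/0.09 = 0.04167n.
- With 2 degrees of freedom, 80% power needs n = 232 per group (noncentrality 9.67). At n = 180 the power is 69%.
- A pairwise two-sided comparison of 15% with 7.5% needs 278 per group.

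So 180 is not reproduced by these standard formulas. The point does not depend on this: 180, 232 and 278 are all far above 20–30.

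**Step 2. Power of the stated test.** For every table (a, b, c) of events, the Fisher p-value is the sum of the probabilities, given the total, of all tables no more probable than the one observed. Power is the binomial probability, at 15%/7.5%/7.5%, of all tables with p ≤ 0.05. Full enumeration gives:

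| Per arm | Power at 5% | Probability of non-significance |
|---|---|---|
| 20 | 6.7% | 93.3% |
| 30 | 11.8% | 88.2% |

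Illustrative tables (sham, active, active): with 20 per arm, 3/0/0 gives p = 0.10 and 4/1/1 gives p = 0.34; with 30 per arm, 5/2/2 gives p = 0.49. With 20 per arm, 15% in sham is 3 events, so even the complete absence of pneumonia in both active arms would not reach 5% at that count.

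**Step 3. Dependence on the assumed rates.** Each row halves the sham rate in both active arms.

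| Sham rate | Source | Power, 20 to 30 per arm |
|---|---|---|
| 7.4% | median, Background | 2–5% |
| 13% | UK audit 2010, Background | 5–10% |
| 15% | example, Weaknesses | 7–12% |
| 16% | UK audit 2008, Background | 7–13% |
| 30% | assumed | 16–26% |
| 45% | top of the range, Background | 29–45% |

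**Step 4. What estimation would show.** For one RMT arm against sham, d = 0.075 − 0.15 = −0.075. The Newcombe interval combines the Wilson limits (l, u) of each proportion:
- lower = d − √[(p₁ − l₁)² + (u₂ − p₂)²]
- upper = d + √[(u₁ − p₁)² + (p₂ − l₂)²]

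20 per arm: Wilson limits 0.018 to 0.269 (RMT) and 0.052 to 0.360 (sham).
- lower = −0.075 − √(0.057² + 0.210²) = −0.29
- upper = −0.075 + √(0.194² + 0.098²) = +0.14

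30 per arm: Wilson limits 0.022 to 0.224 and 0.063 to 0.316.
- lower = −0.075 − √(0.053² + 0.166²) = −0.25
- upper = −0.075 + √(0.149² + 0.087²) = +0.10

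These use expected, partly fractional counts and only indicate the width to be expected.

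**The case against.** The strongest reply has three parts.

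First, the low power is disclosed. The article says a pneumonia end point would need far more participants and chose cough flow as the primary outcome for that reason. A reader so warned is less likely to take non-significance for no effect, and nothing in the article plans such a reading. This stands: the low power is not a hidden error. But the disclosure explains the choice of primary outcome. It does not supply an analysis that answers objective (a) for pneumonia.

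Second, effect measures and interval methods for a secondary binary outcome are commonly left to the statistical analysis plan, and the article describes the ANCOVA outcomes just as briefly. This stands in part. A reader might infer that the trial will produce no estimate at all. The article does not support that: the three incidences must exist before they can be compared, transparent reporting is promised, and further exploratory analyses are allowed. What can be said is that the article specifies no effect estimate or interval. The point remains more than a missing detail, because the article does choose a method for pneumonia, and that method does not yield what the objective asks for. The optional exploratory analyses name no pneumonia estimate. The planned analysis of cough flow against pneumonia is about a surrogate, not a treatment effect.

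Third, the power figure rests on one illustration. This also stands. A reader might call a non-significant result near-certain, but 88–93% applies to a halving from 15%. A halving from 45% gives 29–45% power.

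A reader might also argue that including pneumonia in the Benjamini-Hochberg adjustment penalises the other outcomes. The article does not define the family. If it is the five listed hypotheses, removing one moves the smallest threshold only from 5%/5 = 1.0% to 5%/4 = 1.25%, and taking a listed hypothesis out of the correction is itself debatable. That argument is not relied on here.

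**Conclusion.** The point holds as a mismatch between objective and method, not as a claim that the trial will yield no estimate. The article sets out to determine the magnitude of effect on pneumonia, and the only treatment comparison it states for pneumonia is an omnibus test that gives neither size, direction nor interval.

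The size rests on three assumptions: the article's 15%/7.5%/7.5% example, 20 to 30 analysed per arm, and a 5% level without multiplicity adjustment. Any adjustment that lowers the level would lower the power further. Among the halvings examined, power stays below one half even from the highest incidence quoted for non-intensive-care settings.

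It is a cheap and worthwhile improvement to a secondary outcome. The primary analysis is unaffected.

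**What to change.** Change the pneumonia sentence under Statistical analysis so that:
- the main pneumonia result is the number and proportion with pneumonia per arm from baseline through week 4, and the risk difference of each RMT arm against sham with a 95% confidence interval by a named method suited to small counts, for example Newcombe;
- the three-group Fisher p-value is reported as a supplement;
- the text states that a non-significant result will not be read as absence of effect.

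The cost is a sentence or two in the plan, with no new data and no change to the sample size. The downside is that less weight falls on the formal pneumonia test. The intervals will be wide, roughly 35 to 43 percentage points across at the example rates, and that width is itself useful information for planning the larger trial.
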